### Time‐Table

2.8

Patient recruitment duration: 24 months (23/9/2023–22/9/2025).

### Statistical Analysis

2.9

Basic descriptive tests will be used for qualitative data. Normality will be tested for the quantitative data using the Kolmogorov–Smirnov test. To compare the qualitative data, Pearson's chi‐squared test, and for the comparison of quantitative data, an independent samples t‐test will be used. A binary logistic regression analysis will be performed to determine the predictors of cCR. All analyses will be done in the intention‐to‐treat population. We will also perform subgroup analysis on patients with a cCR who choose a watch‐and‐wait approach after TNT to determine predictors of survival outcomes. Analyses will be done using IBM SPSS Statistics version 26 with a *p* value of 0.05 as the significance boundary.

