**Methods:**

158 patients (18–80 years old) with standard or high‐risk LARC (T3/T4 tumor or lymph node positive) located at least 5 cm from the anal verge will be randomized into two groups: LCRT (with a dose of 50.4 Gy in 28 sessions) or SCRT (with a dose of 25 Gy in five sessions). Both of these groups will receive concurrent chemotherapy (capecitabine 825 mg/m^2^ twice daily) followed by consolidation chemotherapy with the CAPEOX regimen for 6 cycles or mFOLFOX7 for 9 cycles. We will compare the complete clinical response (initially 12–16 weeks after the last RT fraction and eventually 2 weeks after the last chemotherapy cycle) by MRI as the primary endpoint. Overall survival (OS), metastasis‐free survival (MFS), local control, and toxicities will be evaluated after 3–5 years as the secondary endpoints.

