## Methods/Design

2

Patients with locally advanced rectal adenocarcinoma (T3 or T4 primary tumor and/or lymph node‐positive disease), who are referred to the Cancer Institute of Imam Khomeini Hospital Complex, Tehran, from September 2023 to the end of March 2025, will participate in this phase 3, randomized, investigator‐blinded, parallel group study. The initial workup comprises total colonoscopy, contrast‐enhanced thoracoabdominopelvic computed tomography (CT) scan, pelvic magnetic resonance imaging (MRI) with intravenous gadolinium, and routine blood tests including tumor markers (carcinoembryonic antigen [CEA] and cancer antigen [CA] 19–9), complete blood count, as well as liver and renal function tests. An expert radiologist will be assigned to review the MRI images and determine the caudal tumor distance from the anal verge, exact T and N staging per the American Joint Committee on Cancer (AJCC) eighth edition, intactness of the mesorectal fascia, circumferential radial margin (CRM), the exact number, location, and the largest size of the pathologic lymph nodes, presence of extramesorectal lymphadenopathies, and extramural vascular invasion (EMVI). For patients who have a high CEA above 20 ng/mL, a positron emission tomography will be requested to rule out distant metastasis. The mismatch repair (MMR) system will be evaluated by immunohistochemistry on the biopsy specimen for all patients before randomization. Informed consent will be obtained from patients after a thorough explanation of the treatment process; if a patient decides to withdraw from the study, they will be removed and receive the standard protocol treatment. The study protocol was approved by the Research Ethics Committees of Imam Khomeini Hospital Complex–Tehran University of Medical Sciences (TUMS) (approval number: IR.TUMS.IKHC.REC.1401.238).

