#### Secondary Endpoints

2.4.2

Following the completion of treatment, patients will be monitored, and the rates of local, regional, and distant failure will be recorded in 3 and 5 years, respectively. Local recurrence‐free survival, regional recurrence‐free survival, distant metastasis‐free survival, and OS will be evaluated as secondary endpoints, with the last chemotherapy cycle date being the reference time point for survival outcome calculation. We will also perform a subgroup analysis on an MRI‐defined high‐risk group with either of the following features: elevated CEA (> 20 ng/mL), cT4, cN2, positive CRM, presence of EMVI, pathologic extramesorectal lymphadenopathies, and/or large (short axis diameter ≥ 1 cm) mesorectal lymph nodes. Treatment‐related adverse events, including gastrointestinal, genitourinary, hematologic, and skin toxicities, will be graded using the Common Terminology Criteria for Adverse Events (CTCAE) version 5 and compared between the two treatment arms. Throughout the study period, patients will undergo periodic blood tests and physical examinations.

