### Sample Size Calculation

2.7

Considering a predicted cCR rate of 76% as reported in the OPRA trial [18] for the LCRT plus consolidation chemotherapy group, and a cCR rate of 52% in the SCRT plus consolidation chemotherapy as reported by a retrospective study [19], to achieve a 90% power with a two‐sided type I error of 5%, we will require 79 patients in each arm [20]. To compensate for an estimated dropout rate of 20%, we will recruit 95 patients to each study group.

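### The rule that all analyses use the intention-to-treat population also covers the toxicity comparison, which needs a treated-patient safety set (minor, secondary endpoint)

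*Protocol article*

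**What the plan says.** Section 2.9 gives one population rule: "All analyses will be done in the intention‐to‐treat population". It makes no exception for safety, and the article names no treated or safety population.

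Toxicity is one of the comparisons to be made. The abstract says that survival outcomes, local control "and toxicities will be evaluated after 3–5 years as the secondary endpoints". Section 2.4.2 specifies "Treatment‐related adverse events, including gastrointestinal, genitourinary, hematologic, and skin toxicities", and says that these "will be graded using the Common Terminology Criteria for Adverse Events (CTCAE) version 5 and compared between the two treatment arms".

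Two other statements bear on who is counted. Methods/Design says that "if a patient decides to withdraw from the study, they will be removed and receive the standard protocol treatment", and the Consent statement repeats this. Section 2.7 says: "To compensate for an estimated dropout rate of 20%, we will recruit 95 patients to each study group".

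**The concern.** Intention-to-treat is the right population for complete clinical response and the survival endpoints. It fits a comparison of treatment-related harm less well, because such harm depends on what the patient received. Under the stated rule, a patient randomised to an arm who receives no study treatment stays in that arm's toxicity denominator. A patient who is randomised to one schedule and receives the other has any toxicity counted against the schedule not received.

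The trial leaves room for both. Patients and treating physicians are not blinded (section 2.6). Withdrawn patients go on to standard treatment, and the Background describes both approaches as standard of care. At stake is how well the toxicity comparison describes the two schedules as delivered. A diluted difference could make the more toxic schedule look closer to the other than it is.

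**Working it through.** **Does the rule reach toxicity?** Section 2.9 says all analyses. Section 2.4.2 plans a between-arm comparison of adverse events. Read together, the toxicity comparison falls under the rule. This is something the article states, not a detail that it omits.

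**Plan figures.** The article gives no toxicity, non-start or switch rate, so there is no toxicity figure to reproduce. The 79 per arm for the primary endpoint does reproduce with the unpooled two-proportion formula: (1.960 + 1.282)² × (0.76 × 0.24 + 0.52 × 0.48) / 0.24² = 10.51 × 0.432 / 0.0576 = 78.8, so 79. Then 79 × 1.2 = 94.8, so 95. Only the 95 per arm is used below, as the group size.

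**Formula.** Let pL and pS be the toxicity rates by schedule received (long and short course). Let u be the share in each arm with no study treatment and s the share who switch, both equal across arms. Assume that non-starters have no events. The as-randomised rates are:

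- long-course arm: (1 − u − s)·pL + s·pS
- short-course arm: (1 − u − s)·pS + s·pL
- difference: (1 − u − 2s)·(pL − pS)

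**Numbers.** The rates of 40% and 25% are assumed, as are u and s. Power is for 95 per arm, two-sided 5%, by the normal approximation.

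| u | s | As-randomised rates | Difference (points) | Factor | Power |
|---|---|---|---|---|---|
| 0 | 0 | 40.0% vs 25.0% | 15.0 | 1.00 | 0.60 |
| 5% | 0 | 38.0% vs 23.75% | 14.25 | 0.95 | 0.57 |
| 0 | 5% | 39.25% vs 25.75% | 13.5 | 0.90 | 0.51 |
| 5% | 5% | 37.25% vs 24.5% | 12.75 | 0.85 | 0.48 |
| 10% | 10% | 34.5% vs 24.0% | 10.5 | 0.70 | 0.36 |

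The factor does not depend on the assumed toxicity rates; the points and the power do.

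**The no-event assumption.** This is the extreme case and gives an upper bound on how far each arm's rate is diluted. A patient who misses radiotherapy but takes study chemotherapy can still have haematologic or gastrointestinal toxicity. If such patients have events at a common rate r, each arm's rate rises by u·r.

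**Unequal shares.** Here the direction is not fixed.

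- True rate 30% in both arms, non-start in one arm only: 30% × 0.95 = 28.5% at u = 5%, and 30% × 0.90 = 27% at u = 10%. This creates a spurious difference of 1.5 to 3 points.
- 40% vs 25%, 5% non-start only in the more toxic arm: 38 − 25 = 13 points, a smaller difference.
- 40% vs 25%, 5% non-start only in the less toxic arm: 40 − 23.75 = 16.25 points, a larger difference.

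**The case against.** The case on the other side has several parts.

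*The sentence may not be meant literally.* It follows the regression for complete clinical response, and the next sentence announces an analysis of patients who choose watch-and-wait, who are not the intention-to-treat population. An analysis plan that is not shown may define a safety set. That is possible, but such a plan would then depart from the published rule. What needs correcting is the over-broad statement.

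*Withdrawn patients are removed.* If so, some non-starters would not be in the denominator at all. This stands. It means the toxicity denominator is unclear as well as ill-suited, and the two statements need reconciling.

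*Few patients should fail to start.* Radiotherapy comes first in both arms, and inability to receive chemotherapy or radiotherapy is an exclusion. This also stands, and it is why the expected effect is modest.

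*Comparing harms by assigned strategy is legitimate.* It is, and it keeps the randomised comparison, whereas patients who switch may differ in frailty or prognosis. That is a reason to keep the as-randomised table.

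A reader might be tempted to go further in two ways. One is to treat the 20% dropout in section 2.7 as a never-start rate. It is an allowance in the sample size for a response endpoint whose final assessment falls 22–23 weeks after radiotherapy, so dropout may come long after radiotherapy has been given. The other is to say that patients who miss the allocated radiotherapy cannot have an event. The chemotherapy in both arms, and the haematologic and gastrointestinal events listed, rule that out.

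**Conclusion.** The concern holds as a minor point on a secondary endpoint. The stated rule puts toxicity in the intention-to-treat population. That dilutes the rates when patients receive no study treatment and misattributes events when they switch schedule. With equal shares in both arms and no events among non-starters, the difference keeps (1 − u − 2s) of its as-received size: 95% at 5% non-start and 90% at 5% switching each way. The shares and toxicity rates are assumptions, so the real size is unknown. It is zero if nobody fails to start or switches, and modest if few do.

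A reader might infer that the rule always hides harm by pulling the difference toward zero. That follows only when the shares are similar in both arms; unequal shares can shrink, widen or create a difference. A reader might also infer that a main aim of the trial is compromised. The abstract states the objective as comparing complete clinical response and lists toxicities last among the secondary endpoints. Intention-to-treat remains right for efficacy, and the primary result is not affected.

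**What to change.** In section 2.9:

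1. Limit the intention-to-treat rule to the efficacy endpoints.
2. State that toxicity is compared in all patients who received at least one radiotherapy fraction or one dose of study chemotherapy, grouped by the radiotherapy schedule actually received, or by assigned arm if no fraction was given. Requiring a fraction alone would drop patients who took only capecitabine.
3. Give the as-randomised toxicity table as a supplement.
4. Reconcile this with Methods/Design and the Consent statement by saying whether a withdrawn patient is removed from study treatment and follow-up only, or from the analysis as well.

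The cost is a few sentences. The small downside is that the as-received comparison is not strictly randomised, which is why the supplement should stay. Fixing the denominator before the comparison is run also avoids choosing it afterwards.

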**FIGURE 1 cam471472-fig-0001:**
[figure not shown]
Study protocol schema.

Upon completion, patients will be offered TME, unless a complete clinical response is observed on restaging with MRI and rectosigmoidoscopy. If a patient has a near‐complete clinical response, then DRE, MRI, and rectosigmoidoscopy will be repeated in 4–8 weeks. In patients with a final complete clinical response, the possibility of a watch‐and‐wait approach will be discussed with the patients if confirmed in a multidisciplinary tumor board. The watch‐and‐wait protocol consists of three‐monthly assessments by CEA and CA19‐9, pelvic MRI with contrast every 6 months, rectosigmoidoscopy every 4–6 months, and thoracoabdominopelvic CT scans annually for 2 years. After that, all the assessments are done on operated patients up to 5 years.

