#### Primary Endpoint

2.4.1

Complete clinical response (cCR) will initially be assessed by MRI and rectosigmoidoscopy 12–16 weeks following the termination of radiotherapy. A second assessment will be done 2 weeks after all chemotherapy cycles are given (22–23 weeks post‐RT) using digital rectal examination, rectosigmoidoscopy, and MRI. The MRI report must indicate the regression of the tumor and the extent of residual tumor signal on T2 and diffusion‐weighted imaging (DWI) sequences (mrTRG: 1–5 [16]), and rectosigmoidoscopy must show a complete response to therapy (including normal, whitish scar and/or telangiectasia without any ulcer or polypoid tissue or a mass and stenosis [17]). Patients with either a reliable mrTRG score of 4 or 5 at the first assessment will be referred for surgery if they are M0 in re‐staging. Using a PET scan is optional for further evaluation in suspected cases.

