No study has yet prospectively compared SCRT and LCRT, both given with TNT protocols, and this was the rationale for us to design the current study in which we will be comparing the efficacy and toxicities of both SCRT and LCRT, followed by consolidation chemotherapy to determine the best TNT strategy for rectal cancer patients. Due to the present concerns about the re‐growth rate in SCRT patients who achieve a clinical complete response in a report from the Memorial Sloan‐Kettering Cancer Center [30], and the concerning rate of local recurrence in the updated long‐term analysis of the RAPIDO trial [23] we will not be recruiting low‐lying tumors as an extra precaution measure until more convincing evidence is available regarding the noninferiority of SCRT compared with LCRT for organ preservation. A similar study is also being conducted in Germany (ACO/ARO/AIO‐18.1, NCT04246684) [15] with a primary endpoint of 3‐year organ preservation rate and an estimated completion date of 2028.

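### The watch-and-wait survival analysis uses a clock that starts before final cCR is confirmed, in a set selected after randomisation: it needs its own start date and a non-randomised label

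*Protocol article*

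**What the plan says.** Section 2.9 places all analyses in the intention-to-treat population and then adds a "subgroup analysis on patients with a cCR who choose a watch‐and‐wait approach after TNT to determine predictors of survival outcomes". It lists no candidate predictors and gives this analysis no start date of its own.

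Section 2.4.2 fixes one origin for the time-to-event endpoints, "with the last chemotherapy cycle date being the reference time point for survival outcome calculation".

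Membership of the subgroup is settled in stages:
- cCR "will initially be assessed by MRI and rectosigmoidoscopy 12–16 weeks following the termination of radiotherapy" (2.4.1).
- "A second assessment will be done 2 weeks after all chemotherapy cycles are given", which 2.4.1 places at 22–23 weeks after radiotherapy.
- For a near-complete responder, digital examination, "MRI, and rectosigmoidoscopy will be repeated in 4–8 weeks" (2.3, text under Figure 1).
- After a final cCR, watch-and-wait "will be discussed with the patients if confirmed in a multidisciplinary tumor board" (same place).

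Section 2.6 says that patients and treating physicians are not blinded.

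**The concern.** Two separate matters arise.

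**Clock.** A patient enters this set only by being alive, and in practice free of progression, when final cCR is confirmed. Time between the last cycle and that confirmation counts as follow-up, yet no event in it can belong to a member of the set. The gap is longer for those who convert late, so a comparison of late with immediate responders is tilted towards the late ones.

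**Selection.** The set is a subset of each arm, filtered by response and then by a choice made with the arm known. If one arm reaches cCR more often, its responders include less favourable tumours, and an arm contrast within the set loses the protection of randomisation. The Discussion cites "present concerns about the re‐growth rate in SCRT patients who achieve a clinical complete response" as a reason for not recruiting low-lying tumours. A reader is therefore likely to look to watch-and-wait patients for information on how durable cCR is by schedule.

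**Working it through.** The protocol gives no figure for this analysis. The nearest stated figure is the sample size, whose cCR rates are used below.

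**Planning figures (2.7).** With 76% vs 52%, 90% power and two-sided 5%, the unpooled formula gives (1.960 + 1.282)² × (0.76×0.24 + 0.52×0.48) / 0.24² = 10.51 × 0.432 / 0.0576 ≈ 78.8, so 79 per arm, as stated. The recruitment target is 95 per arm.

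**Size of the set, before patient choice.**
- 79 per arm: 79×0.76 = 60 LCRT and 79×0.52 = 41 SCRT, total 101.
- 95 per arm: 72 and 49, total about 122.
- Deaths: the Discussion quotes a 3-year overall survival of 86.5% for the short-course TNT arm of another trial. If that applied here, there would be at most 101×0.135 ≈ 14 to 122×0.135 ≈ 16 deaths.

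**Guaranteed event-free time.**
- Immediate cCR: 2 weeks. Near-complete responders: 2+4 to 2+8 = 6–10 weeks.
- If the cycle date means day 1 of the last cycle: consolidation starts at weeks 2–3 after radiotherapy (2.3), so the last cycle starts at weeks 17–18 (CAPEOX, six 3-week cycles) or 18–19 (mFOLFOX7, nine 2-week cycles). Assessment at weeks 22–23 then leaves 3–6 weeks, or up to 6+8 = 14 with reassessment.
- Against 3 years (156 weeks), 2 weeks is 1.3% and 10 weeks is 6.4%.

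**Effect on absolute survival (assumed hazard 0.05 per year).** Survival 3 years after confirmation is exp(−0.15) = 86.1%. Counted from the last cycle with a guaranteed period g, it is exp(−0.05×(3−g)): 86.2% for 2 weeks and 86.9% for 10 weeks. The gain is 0.2 to 0.8 percentage points.

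**Effect on late versus immediate responders (true ratio 1.00).** With hazard λ and follow-up to F years from the last cycle, expected events per patient are E = 1 − exp(−λ(F−g)) and person-time is g + E/λ, so the observed rate is E / (g + E/λ). With λ = 0.05 and F = 3:
- g = 2 weeks: 0.0493. g = 6 weeks: 0.0479. g = 10 weeks: 0.0466.
- Late/immediate ratio: 0.97 (6 weeks) to 0.94 (10 weeks). At F = 5 it is 0.98 to 0.97.

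This is the distortion of about 5%. It disappears when follow-up starts at confirmation.

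**Effect of the clock on other coefficients.** Cox models were fitted to simulated data with true arm hazard ratio 1, cCR 76%/52%, and a latent factor acting on response (log-odds 1 per SD) and on survival (log hazard 0.7 per SD):
- Adding a constant 2 weeks: log hazard ratio 0.2176 before and 0.2176 after.
- Delays equally distributed in the arms: arm hazard ratio 1.133 from the last cycle, 1.133 from confirmation.
- Near-complete share 50% in one arm and 10% in the other: 1.146 against 1.134.

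**Effect of selection on an arm contrast (LCRT vs SCRT, true ratio 1.00).**
- Model A: responders are the best 76% or 52% on a latent score with correlation ρ to a prognostic factor; hazard 0.05 per year times HR per SD; censoring at 3 years. Rate ratio about 1.05 (ρ 0.3, HR 1.5), 1.13–1.14 (0.5, 2) and 1.34 (0.7, 3).
- Model B: the Cox simulation above, with the factor's effect on response at 0.5, 1 and 2 log-odds per SD. Hazard ratio 1.06, 1.13 and 1.21, and 1.00 when the factor does not affect response.
- Starting the clock at confirmation leaves the Model B values essentially unchanged, so the clock fix does not cure selection.

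**The case against.** **The clock scarcely matters for predictors.** This stands for most of them. Everyone in the set shares the guaranteed time, and a common shift leaves Cox coefficients unchanged. What remains is the effect on absolute estimates and on late versus immediate conversion.

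**Response is already assessed at 12–16 weeks, before time zero.** True, so response is partly known by then. But 2.3 ties watch-and-wait to a final cCR after treatment is complete, so membership is still settled after the origin.

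**Treatment arm is never named as a predictor.** Correct. Section 2.9 lists no predictors and describes no arm comparison in this set, and time to conversion is not named either. The Discussion uses the regrowth concern to justify eligibility; it does not assign that question to this analysis. The selection limb is therefore conditional on arm being examined.

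**Prognosis among watch-and-wait patients is a legitimate question.** It is. Associations within the set are valid as description and mislead only if read causally or as a randomised effect.

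**The selection figures rest on assumptions.** They do. The correlations and hazards are not in the protocol, and the Discussion reports cCR of 46% in both groups of a retrospective comparison; with equal rates the mechanism largely vanishes. With about 15 deaths, the standard error of a log hazard ratio is about √(4/15) ≈ 0.5, so for overall survival the bias is small beside the noise.

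**The detail belongs in a fuller document.** This would answer a complaint about missing predictors. It does not answer the clock, because 2.4.2 states a rule that, applied as written, does not fit this set.

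**Conclusion.** The point holds in a limited form. The stated origin precedes confirmation of final cCR by 2 weeks, or by 6–10 weeks for near-complete responders. It inflates absolute estimates by weeks and flatters late converters by about 5% on the hazard ratio (3–6% at 3 years, less at 5, with an assumed constant hazard of 0.05 per year). Its effect on other coefficients is negligible.

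An arm contrast within the set, if made, would not be randomised. With cCR at 76% vs 52% and the assumed correlations, a true ratio of 1.00 could appear as about 1.05–1.34 to the disadvantage of LCRT.

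Three stronger readings are not supported:
- A reader might infer that the early clock biases the predictors in general. The calculations show that it does not.
- A reader might infer that the protocol plans to settle cCR durability by schedule in this subgroup. It does not say so.
- A reader might see a contradiction with the intention-to-treat statement. The next sentence openly adds a restricted analysis, so it is an exception that has not been labelled.

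**What to change.** In 2.9, add for the watch-and-wait analysis:
- Follow-up starts on the date cCR is confirmed, which for near-complete responders is the date of the repeat assessment.
- The analysis is exploratory and prognostic, and is an exception to the intention-to-treat statement.
- Any contrast between arms within this set is labelled non-randomised. The effect of radiotherapy schedule on survival and recurrence is inferred only from all randomised patients.

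The label is needed as well as the new start date, because the start date does not remove selection. An arm coefficient need not be forbidden if it is labelled in this way. The change takes a few sentences and no new data, since the assessment dates are recorded for the primary endpoint and its reassessment. The downside is a follow-up shorter by 2 to 10 weeks per patient.
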